# Postprandial effect of breakfast glycaemic index on vascular function, glycaemic control and cognitive performance (BGI study): study protocol for a randomised crossover trial

**DOI:** 10.1186/s13063-016-1649-x

**Published:** 2016-10-24

**Keywords:** Glycaemic index, Postprandial period, Vascular stiffness, Blood glucose, Cognition

## Abstract

**Background:**

Postprandial glycaemic response affects cognitive and vascular function. The acute effect of breakfast glycaemic index on vascular parameters is not sufficiently known. Also, the influence of breakfasts with different glycaemic index on cognitive performance has been mostly studied in children and adolescents with varying results. Therefore, the purpose of this study is to analyse the postprandial effect of high and low glycaemic index breakfasts on vascular function and cognitive performance and their relationship with postprandial glycaemic response in healthy young adults.

**Methods/design:**

This is a crossover clinical trial targeting adults (aged 20–40 years, free from cardiovascular disease) selected by consecutive sampling at urban primary care health clinics in Salamanca (Spain). Each subject will complete three interventions with a washout period of one week: a control condition (consisting of water); a low glycaemic index breakfast (consisting of dark chocolate, walnuts, yogurt and an apple, with an overall glycaemic index of 29.4 and an energy contribution of 1489 kJ); and a high glycaemic index breakfast (consisting of bread, grape juice and strawberry jam, with an overall glycaemic index of 64.0 and an energy contribution of 1318 kJ). The postprandial effect will be assessed at 60 and 120 minutes from each breakfast including blood sampling and cognitive performance evaluations. Measurements of arterial stiffness and central haemodynamic parameters will be taken at –10, 0, 15, 30, 45, 60, 75, 90, 105 and 120 minutes.

**Discussion:**

The differences in postprandial glycaemic response due to breakfast glycaemic index could affect vascular parameters and cognitive performance with important applications and implications for the general population. This could provide necessary information for the establishment of new strategies in terms of nutritional education and work performance improvement.

**Trial registration:**

ClinicalTrials.gov: ﻿NCT02616276﻿. Registered on 19 November 2015.

**Electronic supplementary material:**

The online version of this article (doi:10.1186/s13063-016-1649-x) contains supplementary material, which is available to authorized users.

## Background

The glycaemic index (GI) is a measure of the speed with which a carbohydrate is absorbed compared to a reference product (pure glucose) [1, 2]. Diets with a high GI increase the risk of diseases related to lifestyles such as type 2 diabetes mellitus [3, 4]. A recent meta-analysis of 14 prospective studies found that high GI diets are associated with an increased risk of cardiovascular disease (CVD) [5], while a reduction in dietary GI can favourably affect the incidence of coronary disease in women [6]. Low GI diets might reduce the risk of CVD because they decrease postprandial glycaemia with different metabolic effects including differences in insulin sensitivity, circulating lipid concentrations and vascular function [3].

Regarding this latter aspect, the currently accepted gold standard to assess arterial stiffness is the carotid-femoral pulse wave velocity (PWV) [7], which has been related to increased morbidity and mortality in both patients with CVD and healthy individuals [8, 9]. Likewise, the augmentation index (AIx) is a measure of wave reflection and arterial stiffness that has been shown to be a predictor of both future cardiovascular events and all-cause mortality [10]. In this way, the Lifestyles and Vascular Aging (EVIDENT) study [11] analysed the relationship between lifestyle and arterial aging in a sample of 1553 subjects who were free from CVD. We concluded that low GI diets were associated with lower AIx values. In this regard, a reduction in central haemodynamic parameters, AIx and PWV, at 60 minutes from food intake has been reported in healthy adults, perhaps because of an increase in insulin and/or visceral vasodilatation [12]. Another possible explanation for these findings might be the postprandial hypotension that occurs after a meal due to decreased cortisol secretion and activation of the parasympathetic system [13]. For these reasons, although the effects of various macronutrients on vascular function have been explored in a number of studies [14–17], Taylor et al. [12] underlined the importance of analysing the impact of different types of meals on parasympathetic activity, central blood pressure (CBP) and vascular function parameters.

Of particular interest is the carbohydrate (CHO) content of a meal, which changes postprandial glucose and insulin levels and results in varying AIx reductions in postmenopausal women [18]. Thus, breakfast would play a fundamental role, because traditional breakfast foods tend to be high in CHOs, and there can be variability in the GI of these CHOs. It appears that consuming food early in the day can have a beneficial metabolic impact regardless of GI and that low GI meals can be of more value for glycaemic control in the morning than the evening [19]. However, despite the fact that breakfast patterns are associated with metabolic profiles [20], few authors have studied their effect on cardiovascular responses. Ahuja et al. [21] found that a light breakfast (1301 kJ energy) reduced AIx, CBP and blood pressure (BP), and increased heart rate (HR) in adults versus fasting (water). In contrast, a trial aimed to compare the dietary effects of a high GI with a low GI breakfast replacement in obese and overweight individuals reported no differences in BP or insulin concentration between breakfasts together with beneficial changes in fasting glucose after the consumption of a low GI breakfast [22].

On the other hand, increasing evidence has shown that the postprandial glycaemic response also has a potential impact on cognitive function [23]. Due to the importance that cognitive processes have on professional development, there is interest in examining the influence of breakfasts with different GI values on cognitive outcomes in healthy young adults.

Cognitive performance may be influenced by many factors including individual and socioeconomic differences or nutritional and health status [24]. The effect that breakfasts with different GIs may have on cognitive performance has been studied in people with type 2 diabetes mellitus and obesity, but it is not clear that a specific GI breakfast could benefit cognitive processes in these participants [23, 25]. However, various studies conducted on children have explored the relationship between breakfasts consisting of different GI foods and cognitive functions with contrasting results [24, 26–29]. It appears that a low GI breakfast can benefit the immediate [28–30] and delayed [31] verbal memory as well as sustained attention [30] and verbal fluency [32]. A high GI breakfast may confer benefits for selective attention, processing speed and working memory [32]. In addition, consuming different GI carbohydrates at breakfast could modulate cognitive performance, but this effect requires more study [33].

### Objectives

The present study aims to evaluate, in a sample of healthy young adults, the postprandial effect of low and high glycaemic index (GI) breakfasts on vascular function, as measured by central blood pressure, augmentation index and pulse wave velocity and also cognitive performance. The secondary goal is to analyse the association of postprandial glycaemic response with vascular function and cognitive performance for high versus low GI breakfasts.

## Methods/design

### Design and setting

We designed a controlled crossover clinical trial where each subject will complete three interventions (control condition, high GI breakfast and low GI breakfast) with a washout period of one week between each trial. The order will be determined by a randomisation sequence generated using randomization.com software (http://www.randomization.com) (Fig. 1). The SPIRIT checklist is provided as Additional file 1.

**Fig. 1 Fig1:**
[figure not shown]
Flowchart of breakfast glycaemic index study. *BF* breakfast

#### Study setting

The study will be conducted in the primary care health area of Salamanca in “La Alamedilla” Research Unit belonging to the Spanish Network for Preventive Activities and Health Promotion (redIAPP) and the Institute of Biomedical Research of Salamanca (IBSAL).

### Study population

The subjects will be selected by consecutive sampling in the primary care clinics of urban health centres from Salamanca (Spain) between 2015 and 2016.

#### Inclusion criteria

The study targets young adults aged 20–40 years of both sexes who agree to sign the informed consent document.

#### Exclusion criteria

Subjects will be excluded who have a history of cardiovascular events (acute myocardial infarction, stroke, etc.), hypertension, diabetes mellitus, dyslipidaemia, pharmacological treatment for any of these conditions, neurological and/or neuropsychological disease or the consumption of toxic substances. We will also exclude patients with celiac disease and/or those intolerant to lactose, subjects on a low-calorie and/or low-sodium diet, pregnant women or those with any other circumstance that the investigators suggest will interfere with the study procedures.

### Sample size

The primary outcome variable is change in central augmentation index (AIx). The Conduit Artery Function Evaluation (CAFE) study [8] found a reduction in cardiovascular events associated with a decline of 6.5 (5.8, 7.3) points in the AIx. This is the basis of our calculation. The power calculation was a repeated measures design and compared both intervention breakfasts with a control condition with an alpha risk of 0.05 and a beta risk of 0.2. The standard deviation (SD) was 10 with a correlation coefficient between the initial and final measurement of 0.7. Thus, 40 subjects are required to detect a minimum difference of 5 points in the AIx between two intervention breakfasts. A loss to follow-up of 5 % was estimated.

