### Statistical analysis

The normal distribution of variables will be verified using a Kolmogorov-Smirnov test. Quantitative variables will be displayed as the mean ± standard deviation if normally distributed or as the median (interquartile range) if asymmetrically distributed. The data will be quantitated using the repeated measures for analysis of variance (ANOVA) or the Friedman test if the data are non-normally distributed. To compare the differences among the three types of breakfast, the ANOVA test will be used, or the Wilcoxon test if the data are non-normally distributed. We will use the least significant difference (LSD) test as post hoc analysis. The relationship of quantitative variables to each other will be tested using Pearson’s or Spearman’s correlation as appropriate. The effect of the interventions can be modified by conditions such as the last menstruation date. To control the effect of confounders on the study results and to adequately evaluate the effect of the interventions, a multivariate analysis will be performed using the general linear model (GLM) in basic or extended models. The contrasting hypothesis will establish an alpha risk of 0.05 as the limit of statistical significance. The data will be analysed using IBM’s SPSS Statistics for Windows version 23.0 (IBM Corporation, Armonk, NY, USA).

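### The primary outcome is a change in AIx with no stated adjustment for the visit's pre-breakfast AIx, which gives up precision that the planned readings could supply

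*Protocol article*

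**What the plan says.** All references are to the protocol article.

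- **Sample size**, outcome: "The primary outcome variable is change in central augmentation index (AIx").
- **Sample size**, inputs: "The standard deviation (SD) was 10 with a correlation coefficient between the initial and final measurement of 0.7", "with an alpha risk of 0.05 and a beta risk of 0.2". The result is that "40 subjects are required to detect a minimum difference of 5 points in the AIx between two intervention breakfasts", and then "A loss to follow-up of 5 % was estimated".
- **Design and setting**: "each subject will complete three interventions (control condition, high GI breakfast and low GI breakfast) with a washout period of one week". The design is therefore a three-period crossover.
- **Arterial stiffness and central haemodynamic parameters**: AIx is read at −10 and 0 minutes and then eight times up to 120 minutes, at every visit. Each visit thus has two pre-breakfast readings.
- **Statistical analysis**: "The data will be quantitated using the repeated measures for analysis of variance (ANOVA"), with a non-parametric alternative. A general linear model is also planned to control confounders. The only modifying condition named is the date of last menstruation. Pre-breakfast AIx is neither named as a covariate nor ruled out.

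No correlation between AIx readings from different visits is given.

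**The concern.** In a crossover each participant is already their own control, so stable differences between people cancel from the low-versus-high contrast whether or not a baseline is subtracted. What a visit baseline can still remove is variation from one visit to the next. Raw change removes it with a slope fixed at 1, which also brings the full reading-to-reading error of both baselines into the contrast. A model with the visit baseline as covariate estimates the slope instead. If the baseline says little about that day's level, the slope goes towards 0 and little noise is added; if it says a lot, the slope rises.

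At stake is the precision of the primary comparison. The pre-breakfast readings are collected anyway, and the article commits to the less efficient way of using them, or at least to no better one.

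**Working it through.** **Inputs.** From Sample size: SD 10, correlation between initial and final measurement 0.7 (read as within visit, *rw*), difference 5 points, alpha 0.05 (two-sided assumed), power 80%, 5% loss. Not in the article: the between-visit correlation *rb*. It is an assumption here, shown from 0 to 0.7. SDs are taken as equal at all readings.

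**Step 1. Reproduce the stated 40.**
- Variance of the difference between two change scores: 4·SD²·(1 − rw) = 4 × 100 × 0.3 = 120.
- n = (1.96 + 0.842)² × 120 / 25 = 37.67, so 38; 38 / 0.95 = 40. This matches.
- A two-group formula on change, with SD 10·√(2 × 0.3) = 7.746, carries the same variance (2 × 60 = 120) and gives the same 38 and 40.
- Variance 60 would give 19, or 20 with loss. One-sided testing with variance 120 would give 30.

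The planned size therefore corresponds to raw change scores, variance 120.

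**Step 2. Compare with baseline adjustment, one baseline and one postprandial value per visit.**
- Raw change: 4·SD²·(1 − rw) = 120, whatever *rb* is.
- Postprandial value alone: 2·SD²·(1 − rb).
- Baseline-adjusted: 2·SD²·(1 − rb)·[1 − ((rw − rb)/(1 − rb))²]. The fitted slope is (rw − rb)/(1 − rb).

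Example at rb = 0.4: slope 0.3/0.6 = 0.5; adjusted variance 120 × (1 − 0.25) = 90; ratio 120/90 = 1.33.

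| rb (assumed) | Raw change | Post value alone | Adjusted | Raw / adjusted | n before loss, adjusted | Power at 38, adjusted |
|---|---|---|---|---|---|---|
| 0 | 120 | 200 | 102 | 1.18 | 33 | 86% |
| 0.2 | 120 | 160 | 97.5 | 1.23 | 31 | 88% |
| 0.4 | 120 | 120 | 90 | 1.33 | 29 | 90% |
| 0.5 | 120 | 100 | 84 | 1.43 | 27 | 92% |
| 0.6 | 120 | 80 | 75 | 1.60 | 24 | 94% |
| 0.7 | 120 | 60 | 60 | 2.00 | 19 | 98% |

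Raw change needs 38 and has 80% power with 38 completers in every row (normal approximation). A paired t calculation gives 78% for raw change and 97% for adjustment at rb = 0.7. Simulation at rb = 0.7 and 0.4 gave adjusted variances of 59.9 and 90.2, in agreement.

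**Step 3. Average the two pre-meal readings**, keeping one postprandial value and correlation 0.7 between all readings of a visit.
- Variance of the mean baseline: 100 × (1 + 0.7)/2 = 85.
- Raw change contrast: 2 × (100 + 85 − 2 × 70) = 90.
- Adjusted: 200(1 − rb) − [2(70 − 100rb)]² / [2(85 − 100rb)].

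| rb (assumed) | Adjusted | Raw / adjusted |
|---|---|---|
| 0 | 200 − 140²/170 = 84.7 | 1.06 |
| 0.4 | 120 − 60²/90 = 80 | 1.13 |
| 0.5 | 100 − 40²/70 = 77.1 | 1.17 |
| 0.6 | 80 − 20²/50 = 72 | 1.25 |
| 0.7 | 60 − 0 = 60 | 1.50 |

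Averaging postprandial readings as well would move the ratio again (1.16 to 5 if all eight are averaged and reading errors are independent), with high power either way. The direction does not reverse.

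**The case against.** Several objections are fair.

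- **Doubling is not the plan's own figure.** A reader might take the stated 0.7 and infer that raw change doubles the variance. But the article describes "a correlation coefficient between the initial and final measurement of 0.7", and readings a week apart need not agree as closely as readings within one seated session. Doubling is the top of the range and rests on an assumption. This objection stands.
- **The baseline is not useless.** A reader might infer that subtracting it loses precision for nothing, so that postprandial values alone would do better. That fails when rb is below 0.4, where raw change beats unadjusted postprandial values. This stands too, and it is why the remedy is adjustment and not dropping the baseline.
- **The trial is not underpowered on this account.** The 40 subjects were derived with variance 120, so adjustment only adds power. This stands.
- **Naming change as the outcome is not itself an error, and the general linear model could hold a baseline term.** Once the visit baseline is a covariate, change and postprandial value give the same breakfast contrast. The article is condensed, and a covariate list may sit elsewhere. This stands in part: the documents do not say that baseline is excluded. But the outcome and the sample size both point to raw change, and the analysis section names another modifier while leaving out this one.

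**Conclusion.** The concern holds as a loss of efficiency. The article defines the primary outcome as a change, sizes the trial on the variance of a raw change-score contrast, and names no adjustment for the visit's pre-breakfast AIx. Under SD 10 and within-visit correlation 0.7, raw change is less precise than the adjusted contrast at every between-visit correlation from 0 to 0.7. The variance ratio is 1.2 to 1.6 for correlations of 0 to 0.6 with single readings, and 2.0 only at 0.7. With the two pre-meal readings averaged against one postprandial reading it is about 1.1 to 1.5 for correlations of 0.4 to 0.7.

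These sizes depend on a between-visit correlation that the article does not give, on equal SDs, and on how the baseline and postprandial values are summarised. The advantage of adjustment is a large-sample result. In a two-visit regression with 38 pairs, estimating the slope adds roughly 1/(38 − 3), or 3%, to the adjusted variance, so at the lowest correlations with averaged baselines the gain is small. No bias, inflated error rate or shortfall in the planned power follows.

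**What to change.** Prespecify that the primary breakfast contrast in AIx is estimated in a within-participant model with the same visit's pre-breakfast AIx, the mean of the −10 and 0 minute readings, as covariate. Enter it as two terms: the participant's mean baseline over visits, and the visit's deviation from that mean. Only the deviation bears on the within-person contrast. The outcome can remain change or be the postprandial value, since the adjusted contrast is the same. Report raw change descriptively, and state the between-visit correlation assumed in any revised precision calculation.

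The cost is one or two model terms and a sentence of text, with no new measurements or participants. The article reports that recruitment is under way and that the analysts will be blinded to the interventions, so the choice can still be fixed before the results are known.

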### Study procedures

On arrival at the research unit, subjects will be weighed, and their height, waist circumference and hip circumference will be measured. Participants will be seated and remain in this position throughout the visit. After 5 minutes of rest, a peripheral blood pressure measurement will be performed, and immediately the central blood pressure and haemodynamic parameters will be obtained. Next, cognitive performance will be assessed, fasting blood samples will be collected and central blood pressure and haemodynamic parameters will be determined again. Subjects will be provided with a randomly assigned breakfast to be consumed within 10 minutes. At the first bite, a timer will be started and additional measurements of central blood pressure and haemodynamic parameters will be taken every 15 minutes. Furthermore, another two cognitive performance evaluations and postprandial blood sampling will be completed at 60 and 120 minutes. Figure 2 shows the Standard Protocol Items: Recommendations for Interventional Trials (SPIRIT) diagram for the trial procedure.

**Fig. 2 Fig2:**
[figure not shown]
SPIRIT diagram. * Randomly assigned breakfast

### Intervention

Each of the three scheduled visits will last 2 hours, 40 minutes; this will occur between 8:15 am and 10:55 am. Participants will be asked to fast for 12 hours overnight prior and to limit their physical activity, alcohol consumption and smoking during the previous 24–48 hours.

#### Nutritional composition of each intervention arm

The nutritional composition of each intervention arm is described as follows:Control condition (BF-1):This will consist of 350 mL of water served at room temperature.High glycaemic index breakfast (BF-2):This will consist of 350 mL of water served at room temperature, 200 mL of grape juice (with 569 kJ/136 kcal), 40 g of white bread (2 slices of 218 kJ/52 kcal each) and 29 g of strawberry jam (with 313 kJ/75 kcal), providing a total of 1318 kJ/315 kcal. The nutrient composition of this meal is 72.0 g (91.4 %) carbohydrate, 0.9 g (2.6 %) fat, 3.9 g (5 %) protein and 1.6 g (1 %) fibre, with an overall GI of 64.0.Low glycaemic index breakfast (BF-3):This will consist of 350 mL of water served at room temperature, a 150-g apple (with 339 kJ/81 kcal), a 125-g low-fat natural yogurt (with 234 kJ/56 kcal), 3 shelled walnuts (with 163 kJ/39 kcal per unit) and 17.5 g of 72 % dark chocolate (with 427 kJ/102 kcal), supplying a total of 1489 kJ/356 kcal. The nutrient composition of this meal is 31.5 g (35.4 %) carbohydrate, 19.9 g (50.3 %) fat, 9.7 g (10.9 %) protein and 6.0 g (3.4 %) fibre, with an overall GI of 29.4.

### Blinding strategy

Because of the nature of the interventions, participants and research staff cannot be blinded. However, those responsible for statistical analysis will be blinded to the interventions.

### Variables and measurement instruments

#### Sociodemographic variables

At the time of study entry and prior to the first intervention visit, data on age, gender, marital status, educational level and occupation will be collected.

#### Lifestyle-related variables

The following lifestyle-related variables will be collected at the time of study entry and prior to the first intervention visit:Smoking:This will be measured using a questionnaire on smoking history and tobacco consumption pattern.Alcohol consumption:This will be measured using a questionnaire on alcohol consumption in the past 7 days specifying drinks and their volumes.Regular diet:This will be assessed with the Diet Quality Index (DQI) [34], which is a validated questionnaire that records the frequency of food intake and assigns a score ranging from 18 to 54 points.Regular physical activity:This will be evaluated with the short version of the International Physical Activity Questionnaire (IPAQ) [35], validated for a Spanish population. It assesses activity in the last 7 days differentiating between three types (walking, moderate-intensity and vigorous-intensity activity), according to the energy expenditure estimated for each of them (3.3, 4 and 8 metabolic equivalents of task [MET], respectively). It allows the MET-minutes/week to be calculated and subjects to be classified according to three activity levels (low, intermediate and high).

